#### Trial Procedures

The following is an outline of the procedures to be performed at each patient visit (see Table 2):ScreeningsInformed consentDemographics/medical historyPhysical examVital signs, height, weightPost-prostatectomy PSAPelvic MRIBone or PET scanProstate 22-gene testUrodynamic testing (optional)EPICInternational Prostate Symptom Score (IPSS)European Quality of Life 5 Dimension (EQ-5D)Common Terminology Criteria for Adverse Events version 5.0 (CTCAE v5.0)First Day of RTWhole blood, serum, plasmaEPICIPSSEQ-5DCTCAE v5.0Last Day of RTWhole blood, serum, plasmaEPICIPSSEQ-5DCTCAE v5.0Follow-up at 3 monthsPhysical examPost-prostatectomy PSA  EPICIPSSEQ-5DCTCAE v5.0Follow-up at Q6 months for 2 yearsPhysical examVital signs, height, weightPost-prostatectomy PSAUrodynamic testing (optional)EPICIPSSEQ-5DCTCAE v5.0Follow up at Q12 months for 3 yearsPhysical examVital signs, height, weightPost-prostatectomy PSAUrodynamic testing (optional)EPICIPSSEQ-5DCTCAE v5.0

**Table 2 Tab2:** Schedule of trial events

Procedure	Screening	First Day of RT	Last Day of RT	FUP at 3mo post-RT	FUP at 6/12/18mo post-RT	FUP at 36/48/60mo post-RT
Informed Consent	X					
Demographics/Medical History	X					
Physical Exam	X			X	X	X
VS, Height, Weight	X			X	X	X
Post-Prostatectomy PSA	X			X	X	X
Pelvic MRI	X					
Bone or PET Scan	X					
Prostate 22-Gene Test	X					
Whole Blood, Serum, Plasma		X	X			
Urodynamic Testing (optional)	X				X	X
EPIC	X	X	X	X	X	X
IPSS	X	X	X	X	X	X
EQ-5D	X	X	X	X	X	X
CTCAE v5.0	X	X	X	X	X	X

*RT* salvage radiotherapy, *FUP* follow up visit, *mo* months, *CTCAE* Common Terminology Criteria for Adverse Events version 5.0

#### Definition of disease assessments

Biochemical failure: two definitions of biochemical failure will be assessed:◦ Primary: PSA ≥ 0.4 ng/mL and rising or initiation of salvage hormones◦ Alternate: PSA ≥ PSA nadir + 2 ng/mL where nadir is the lowest post-RT PSA levelLocal failure: development of a new biopsy-proven mass in the prostate bed, after enrollment in the protocolRegional failure: radiographic evidence (CT or MRI) of lymphadenopathy within the pelvis (lymph node size ≥ 1.5 cm in the short axis) in a patient without the diagnosis of a hematologic/lymphomatous disorder associated with adenopathyDistant metastases: radiographic evidence of hematogenous spread (*e.g.,* bone scan, CT, MRI)Progression: first occurrence of biochemical failure, local failure, regional failure, distant metastasis, initiation of salvage ADT

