#### Secondary endpoints

1. Compare patient-reported GI symptoms using the EPIC questionnaire at the end of RT and 3, 6, 12, and 60 months from end of treatment.2. Compare patient-reported GU symptoms using the EPIC questionnaire at the end of RT and 3, 6, 12, and 60 months from end of treatment.3. Compare time to progression (TTP) where progression is defined as the first occurrence of biochemical failure (BF), local failure, regional failure, distant metastasis (DM), institution of new unplanned anticancer treatment, or death from prostate cancer (PCSM).4. Compare freedom from biochemical failure (FFBF) and TTP rates with an alternate PSA ≥ PSA nadir + 2 ng/mL definition of BF.5. Compare local failure, regional failure, salvage therapy (*i.e.,* institution of new unplanned anticancer treatment), DM, PCSM, and overall survival (OS) rates.

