##### Analysis of secondary endpoints:

Secondary safety endpoints: Between treatment arms differences in each safety endpoints measured as change in domain specific EPIC scores at a specific time points (*i.e.,* end of RT, 3, 6, 12, 24, and 60 months) from base line will be evaluated using t-test or Wilcoxon rank sum test whichever is more appropriate. The domain specific EPIC scores measured over time will also be modeled using a linear mixed effects model with fixed effects including time points, treatment arm, Gleason score, baseline PSA, T-stage, age, race, and a random intercept. Between treatment arms differences in GI and GU EPIC scores at 2 years adjusting for baseline scores and other covariates will be assessed using analysis of covariance (ANCOVA). Results from the primary unadjusted analysis and covariates adjusted analysis are expected to lead to similar conclusions. Otherwise, further investigation concerning possible heterogeneous subgroup effects and/or the impacts of missing values will be carried out to ensure that meaningful conclusions can be made.Secondary efficacy endpoints: For competing-risk endpoints such as PCSM, local failure (LF), regional failure (RF), TTP, and DM, Gray’s cumulative incidence method will be used with death as a competing risk for LF, RF and DM and death not due to prostate cancer for PCSM and TTP. OS and FFBF will be estimated by the Kaplan–Meier method and compared between arms with the log-rank test. Cox regression will be used to obtain hazard ratios (HRs) for OS and TTP. Fine and Gray’s regression will be used for the endpoints with competing risks. Adjusted HRs and the respective 95% confidence interval will be computed. Baseline PSA, stratification variables (baseline EPIC score and ADT status), age, race, and other covariates (Gleason, T-stage), will be adjusted for as appropriate in this analysis.

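### The alternate biochemical-failure definition has no salvage-hormone event, so freedom from biochemical failure under that definition is biased upward

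*Protocol article*

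**What the plan says.** The section Definition of disease assessments gives two definitions of biochemical failure and says that both will be assessed. The first is "Primary: PSA ≥ 0.4 ng/mL and rising or initiation of salvage hormones". The second is "Alternate: PSA ≥ PSA nadir + 2 ng/mL where nadir is the lowest post-RT PSA" level, with no treatment component and no limit on when the nadir may be taken.

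Item 4 under Secondary endpoints applies the second definition: "Compare freedom from biochemical failure (FFBF) and TTP rates with an alternate PSA ≥ PSA nadir + 2 ng/mL definition of BF". The section Analysis of secondary endpoints gives the method: "OS and FFBF will be estimated by the Kaplan–Meier method and compared between arms with the log-rank test". It has no rule for a man who starts salvage hormones before meeting the PSA criterion.

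Two related endpoints handle salvage treatment separately. TTP (Secondary endpoints, item 3) includes "institution of new unplanned anticancer treatment, or death from prostate cancer (PCSM") among its events, and the definitions section lists "Progression: first occurrence of biochemical failure, local failure, regional failure, distant metastasis, initiation of salvage ADT". Item 5 also compares salvage therapy as an endpoint of its own ("Compare local failure, regional failure, salvage therapy").

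**The concern.** Salvage hormones lower PSA. An endpoint based on PSA alone therefore stops working as a measure of relapse once they start. The primary definition deals with this by making the start of hormones an event. The alternate needs that clause more, because its threshold is higher and leaves a longer window in which salvage can come first. With a near-zero nadir, the primary definition is met at 0.4 ng/mL and rising, while the alternate waits for about 2 ng/mL. A man treated in that window has relapsed and been treated for it, yet alternate-definition FFBF records no failure at that time.

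Alternate-definition FFBF is a named secondary efficacy comparison. As written, its curves would partly describe when salvage was started and not only how well radiotherapy controlled the disease.

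**Working it through.** **Events under each endpoint.** Take a man whose PSA falls below 0.1 ng/mL after radiotherapy, rises to 0.7 and is then treated with salvage hormones.

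- Primary-definition failure: event, by PSA and again by hormone start.
- TTP under either definition: event, through its own salvage-treatment component.
- Salvage-therapy endpoint: event.
- Alternate-definition FFBF: no event. His PSA is below about 2.1, and treatment now suppresses it.

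Only the last endpoint misses him.

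**The nadir clause.** The lowest PSA after radiotherapy is not limited to values before salvage, so a suppressed value can become the nadir. A lower nadir lowers the threshold, so this does not by itself add to the overstatement. It means that any later event is measured from a treated PSA.

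**Size if treated men stay at risk.** The documents give no failure rate or salvage rate, and the plan has no FFBF figure to reproduce. Its sample size rests on EPIC change scores. The inputs below are assumptions, except 68 per arm (Sample size and accrual).

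- p: share of men failing under the primary definition by 5 years, assumed 20–40%.
- q: share of those men who start hormones before nadir + 2, assumed 25–75%.
- u: share of those early-treated men who still reach nadir + 2 by 5 years, unknown.
- a: share of all men who reach nadir + 2 without earlier hormones.

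Every man who starts salvage hormones is a primary-definition failure, so the early-treated share of all men is p × q. Then:

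- FFBF with the hormone event = 1 − (a + pq)
- FFBF as written = 1 − (a + pqu)
- Overstatement = pq(1 − u), which is at most pq

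The term a cancels, so nothing has to be assumed about the men who are not treated early. With u = 0:

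| p | q = 25% | q = 50% | q = 75% |
|---|---|---|---|
| 20% | 5 points (3.4 men per arm) | 10 (6.8) | 15 (10.2) |
| 30% | 7.5 (5.1) | 15 (10.2) | 22.5 (15.3) |
| 40% | 10 (6.8) | 20 (13.6) | 30 (20.4) |

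Men per arm = 68 × p × q. If half of the early-treated men later reached nadir + 2 (u = 0.5), each entry would halve; the middle cell would be 7.5 points.

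**Size if treated men are censored at hormone start.** Let r be the 5-year risk with the hormone event included and s the share of those events that are hormone starts. With proportional cause-specific hazards, Kaplan–Meier with censoring estimates (1 − r)^(1 − s) and not 1 − r.

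- r = 0.20, s = 0.25: 0.846 − 0.800 = 4.6 points
- r = 0.30, s = 0.50: 0.837 − 0.700 = 13.7 points
- r = 0.40, s = 0.75: 0.880 − 0.600 = 28 points

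Censoring therefore does not remove the problem. It is informative because hormones are started in response to relapse.

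**The case against.** The strongest reply is that these men are not lost to the trial. Primary-definition failure, both versions of TTP and the separate salvage-therapy comparison all count them. That stands, and it confines the problem to one endpoint. A reader might infer that the omission could hide a loss of efficacy with 5 fractions. The documents do not support that, since such a loss would still show in those other endpoints.

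A PSA-only alternate could also be a deliberate sensitivity definition. That is possible, but the article does not say so, and the endpoint would still be distorted by a PSA-lowering treatment. Handling of treated men may be set out in a fuller document. However, the event definition itself is written out here, and neither keeping these men at risk nor censoring them gives an unbiased curve.

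Adding hormone start as an event does not remove clinical discretion, because the event date would then depend on when salvage begins. This also stands. It is a real trade-off, and one the primary definition already accepts.

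Three further inferences should be resisted:

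- **A corrected level.** With p = 30% and q = 50%, one might say that FFBF reads 85% when the truth is 70%. That treats every primary-definition failure as a failure under the corrected alternate. Men whose PSA stays between 0.4 and nadir + 2 without hormones fail under neither version of the alternate, so only the gap can be stated, not the levels.
- **A spurious difference between arms.** Equal relapse of 30% with early salvage of 25% in one arm and 75% in the other would give 0.30 × 0.50 = 15 points. No blinding is described, so different salvage timing is conceivable, but nothing in the article indicates such a split or its direction.
- **Disagreement between FFBF and TTP.** TTP is a broader composite and may differ from FFBF by design.

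**Conclusion.** The point holds for alternate-definition FFBF alone. As written, men who start salvage hormones before nadir + 2 are not failures at salvage, so the estimate is too high if they stay at risk. If they are censored, the censoring is informative.

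The upward direction follows from the text and from the fact that hormones lower PSA. The size does not: at most about p × q, or 5 to 30 percentage points over the assumed ranges, and less to the extent that treated men later reach nadir + 2. No level of FFBF and no between-arm bias can be derived from the documents.

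No primary endpoint, design figure or primary conclusion changes. Severity is minor to moderate.

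**What to change.** In Definition of disease assessments, make the alternate event the earlier of (a) PSA at or above nadir + 2 ng/mL and (b) the start of salvage hormones. Define the nadir as the lowest PSA after radiotherapy and before any salvage therapy. Use this event for the alternate-definition FFBF comparison in Secondary endpoints, item 4, and in Analysis of secondary endpoints. If a PSA-only version is wanted, keep it as a labelled sensitivity analysis.

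The cost is one line of wording. The date of hormone start is already needed for the primary definition. Alternate-definition FFBF will look less favourable, and its event date will partly reflect when clinicians start salvage, as it already does under the primary definition. The change concerns an endpoint definition only and implies nothing about when salvage should be given.

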#### Inclusion criteria

Men aged ≥ 18 with histologically confirmed prostate cancer after prostatectomy with detectable PSA. Patients with detectable post-prostatectomy PSA whether (1) persistently detectable post-operatively or (2) developing biochemical recurrence after prostatectomy (initially undetectable) are eligible. Patients with early BCR or persistently detectable PSA after prostatectomy must wait a minimum of 6 months post-prostatectomy but can initiate ADT as indicated. PSA does not need to be detectable for men with pathologically node positive disease.KPS ≥ 70Patient with no evidence of distant metastatic disease on positron emission tomography (PET)/CT/MRI or bone scan < 90–180 days prior to enrollment. Patients with positive pelvic lymph nodes are eligible.Ability to receive MRI-guided radiotherapyEquivocal evidence of metastatic disease outside the pelvis on standard imaging requires documented negative biopsyAbility to complete the EPIC questionnaire

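### The regional failure rule has no biopsy route for pelvic nodes under 1.5 cm and does not require the enlarged node to be new or progressing

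*Protocol article*

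**What the plan says.** Definition of disease assessments fixes regional failure as "radiographic evidence (CT or MRI) of lymphadenopathy within the pelvis (lymph node size ≥ 1.5 cm in the short axis"), with an exclusion for patients whose adenopathy goes with a blood or lymphatic disorder. Modality, threshold, axis and exclusion are all stated. Histology, PET, and a requirement that the node be new or have grown are not.

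The neighbouring definitions are built differently. Local failure needs a new, biopsy-proven mass in the prostate bed. Distant metastasis is "radiographic evidence of hematogenous spread", with an open list of imaging methods.

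Under Inclusion criteria, "Patients with positive pelvic lymph nodes are eligible", with no size limit given.

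Regional failure is compared between arms in its own right (Secondary endpoints: "Compare local failure, regional failure, salvage therapy"). For the analysis, "Gray’s cumulative incidence method will be used with death as a competing risk for LF, RF and DM".

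Progression is listed twice. Secondary endpoints ends its list with "institution of new unplanned anticancer treatment, or death from prostate cancer (PCSM"). Definition of disease assessments gives "first occurrence of biochemical failure, local failure, regional failure, distant metastasis, initiation of salvage ADT".

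**The concern.** Regional failure is the endpoint that describes pelvic nodal control, and the two arms use different nodal schedules in patients who receive nodal treatment. If the rule is followed as written, a relapse in a pelvic node proven by tissue but smaller than 1.5 cm is recorded as no regional failure. The size rule can also be met by a node that was already large before treatment. The first gap removes real events and the second can add events that are not failures. Either way, the reported cumulative incidence would not describe what its name says.

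What is at stake is one secondary efficacy comparison and, through the two unequal progression lists, possibly a few progression events. The co-primary EPIC change scores and the sample size do not depend on it.

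**Working it through.** The documents state no regional failure rate, event count or power, so there is no figure of the plan to reproduce. The check is a reading of the definitions, followed by an illustration on assumed values.

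**1. A small proven relapse.** Take a hypothetical man with a biopsy-proven 1.0 cm pelvic node after radiotherapy, who then receives new treatment.

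- Regional failure: no, since 1.0 cm is below 1.5 cm and biopsy is not a listed route.
- Local failure: no, since the site is not the prostate bed.
- Distant metastasis: no, since a pelvic node is not hematogenous disease.
- Biochemical failure (primary definition): yes, if "PSA ≥ 0.4 ng/mL and rising or initiation of salvage hormones" applies.
- Salvage therapy, as its own secondary endpoint: yes, if the treatment was new and unplanned.
- Progression in Secondary endpoints: yes, through the new-treatment clause.
- Progression in Definition of disease assessments: only if PSA failed or the treatment was salvage ADT. A node treated otherwise, without PSA failure, is progression under one list and not under the other. That list also omits death from prostate cancer.

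No site-of-failure endpoint records him. Only death is named as a competing event for regional failure, so he stays at risk and counts as free of it unless a node later measures 1.5 cm on CT or MRI. Table 2 lists pelvic MRI and bone or PET scan at screening only, so a later measurement depends on unscheduled imaging.

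**2. A node already large at entry.** Take a hypothetical man who enters with a 1.6 cm pelvic node. Any on-study CT or MRI that still shows it at 1.5 cm or more meets the words of the rule, even if the node has not grown.

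**3. Illustration.** N = 136 comes from Sample size and accrual. Everything else is assumed: R is the true pelvic nodal relapse rate, s is the share proven and treated below 1.5 cm that never reaches it, and k is the number of men counted only because of a node enlarged at entry.

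Counted events = 136 × R × (1 − s) + k. With k = 0:

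| R | True events | s = 25% | s = 50% | s = 75% |
|---|---|---|---|---|
| 5% | 6.8 | 5.1 | 3.4 | 1.7 |
| 10% | 13.6 | 10.2 | 6.8 | 3.4 |
| 15% | 20.4 | 15.3 | 10.2 | 5.1 |

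The loss is cancelled when k = 136 × R × s. At R = 10% and s = 50% that is 6.8, so about seven men with entry nodes still at 1.5 cm or more would offset it. Over the table, the break-even k runs from 136 × 0.05 × 0.25 = 1.7 to 136 × 0.15 × 0.75 = 15.3. The documents give neither s nor k, so the sign of the net error is open.

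**4. Precision.** With events split evenly, the 95% interval around a hazard ratio spans a factor of exp(1.96 × 2/√d) either way, for d events in total.

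- R = 10%: d = 13.6 gives exp(1.063) = 2.9, and d = 6.8 gives exp(1.503) = 4.5.
- R = 15%: d = 20.4 gives 2.4, and d = 10.2 gives 3.4.

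The interval is wide under either definition.

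**The case against.** The strongest reply is that a measurable size threshold is a legitimate, objective choice for a secondary endpoint, and that entry and failure criteria need not match. That stands. At entry, PET is one way to show absence of distant disease, and biopsy serves to rule out equivocal disease outside the pelvis. Neither sets a standard for nodal relapse on study, so the documents do not contradict themselves here. It also stands that the hazard ratio would say little under any definition, so lost precision is not the reason to act. The reason is that a proven event is put in the wrong category.

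Four stronger readings are tempting, and the documents do not support them:

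- *Such a relapse can never be a regional failure.* It becomes one, only later, if a node reaches 1.5 cm on CT or MRI.
- *The regional failure rate is understated.* The missing requirement for a new or progressing node pushes the other way, and no input fixes the balance.
- *The comparison is biased.* The same rule holds in both arms, and nothing shows different misclassification.
- *PET findings should count.* Entry staging may be by bone scan, so some men have no PET to compare with. No follow-up imaging is scheduled, and 5 and 20 fractions are visibly different, so PET-only events would depend on discretionary work-up. This is a matter of judgement.

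One might also say that an article condenses the full protocol. Here, however, the article prints a complete operational rule, and that rule is what is questioned.

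**Conclusion.** The point holds in a limited form. As written, the rule leaves a treated, biopsy-proven pelvic nodal relapse below 1.5 cm outside every site-of-failure endpoint unless a node later reaches the threshold, and it allows a node already enlarged at entry to count. Both follow from the wording and need no assumption. The size and net direction cannot be derived, and all event counts shown rest on assumed values. The effect falls mainly on one secondary endpoint. Biochemical failure, salvage therapy and time to progression as listed under Secondary endpoints can still capture treated patients. This is a cheap improvement in an endpoint definition and does not threaten the trial's main conclusion.

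**What to change.** In Definition of disease assessments, define regional failure as the first of:

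- (a) a biopsy- or cytology-proven pelvic nodal recurrence of any size after enrollment;
- (b) the existing CT/MRI criterion of at least 1.5 cm in short axis, for a node that is new or has progressed since the entry scan.

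Keep the current size-only definition as a sensitivity analysis. Leave PET-only findings optional. If they are admitted, say how a patient without an entry PET is handled. Reconcile the progression list in that section with the one under Secondary endpoints, so that time to progression has a single definition.

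The cost is a sentence or two, a case-report-form field for how the node was confirmed and whether it was present at entry, and one extra analysis. No additional scan or biopsy is needed: limb (a) uses results already obtained, and Table 2 already places a pelvic MRI at screening as the comparator for limb (b). The drawbacks are slightly less direct comparability with trials that use a size-only rule, which the sensitivity analysis covers, and some dependence on discretionary biopsy.

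### The disease-assessment section defines progression more narrowly than the endpoint list, leaves extra-pelvic nodal relapse outside both regional failure and distant metastasis, and lets a persisting baseline node count as regional failure

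*Protocol article*

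**What the plan says.** Progression is defined twice in the protocol article.

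- Secondary endpoints, item 3, lists biochemical, local and regional failure and ends with "distant metastasis (DM), institution of new unplanned anticancer treatment, or death from prostate cancer (PCSM".
- Definition of disease assessments says "Progression: first occurrence of biochemical failure, local failure, regional failure, distant metastasis, initiation of salvage ADT". It names neither prostate-cancer death nor any new treatment other than salvage ADT.

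The latter section also fixes the components. Primary biochemical failure is "PSA ≥ 0.4 ng/mL and rising or initiation of salvage hormones". Local failure must be a new, biopsy-proven mass arising after enrollment. Regional failure is pelvic lymphadenopathy on CT or MRI, with a node of at least 1.5 cm in short axis. Distant metastasis is radiographic evidence of hematogenous spread.

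The inclusion criteria state "Patients with positive pelvic lymph nodes are eligible", with no size limit.

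Analysis of secondary endpoints opens its efficacy part with "For competing-risk endpoints such as PCSM, local failure (LF), regional failure (RF), TTP, and DM" and assigns these to Gray's cumulative incidence. The competing event is "death not due to prostate cancer for PCSM and TTP". It then says "Cox regression will be used to obtain hazard ratios (HRs) for OS and TTP" and gives Fine and Gray's regression to endpoints with competing risks.

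**The concern.** Item 5 of Secondary endpoints compares local failure, regional failure, distant metastasis and prostate-cancer death separately, and item 3 combines them in TTP. Each comparison depends on assigning every patient's first event by rule. Here the rules conflict in one place, leave a gap in a second and lack a baseline reference in a third. Two analysts who followed different sections would count different TTP events. An analyst who followed the component definitions literally would leave some relapses out of both site-specific endpoints, and could score as failure a node that was there at entry.

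With 136 randomized patients, efficacy events may be few, so a handful of re-classified events could matter. If the choice is made once outcomes are known, it is open to the charge of selection.

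**Working it through.** No stated figure is in question, so the check sets the rules side by side.

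**1. Progression as a first event**

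| First event | Secondary endpoints, item 3 | Definition of disease assessments |
|---|---|---|
| Biochemical, local or regional failure, or distant metastasis | event | event |
| Salvage ADT | event, as new unplanned treatment | event, already inside primary biochemical failure |
| New unplanned treatment other than ADT | event | not an event |
| Prostate-cancer death, no earlier recorded failure | event | not an event |
| Death from another cause | competing | competing |

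The two lists are nested: every event in the second column is also an event in the first. They part only in the third and fourth rows. In the fourth row, the analysis section allows only deaths not due to prostate cancer to compete, so under the narrower list that death has no status at all. The competing-risk rule is complete only with the item 3 definition.

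**2. Nodal relapse by site**

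- Within the pelvis, at least 1.5 cm: regional failure.
- Outside the pelvis: not regional failure (wrong site) and not distant metastasis (lymphatic rather than hematogenous).
- Route into TTP: still open through PSA, salvage hormones or, under item 3, any new unplanned treatment.

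The gap therefore falls mainly on the separate regional-failure and distant-metastasis endpoints.

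Its size can only be assumed. Let s be the share of first distant relapses that are extra-pelvic nodal only, and r the share of those that later show hematogenous spread within follow-up. The proportion of distant-metastasis events lost is s × (1 − r). Taking s from 5% to 20% as an assumption:

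- r = 0: 5% to 20% lost
- r = 0.5: 2.5% to 10% lost
- r = 1: none lost, but each such event is dated late

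**3. Baseline nodes**

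Local failure carries two safeguards, newness and onset after enrollment. Regional failure carries neither. For a baseline node to be scored as failure, three things must hold: it measures at least 1.5 cm in short axis at entry, it still does after treatment, and it is imaged. Table 2 schedules pelvic MRI and bone or PET scan at screening only, so the imaging would be unscheduled. The documents do not say how many patients would meet all three.

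**4. Regression for TTP (minor)**

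Cox is named for TTP, and Fine and Gray applies to competing-risk endpoints, which include TTP. To see whether the choice matters, assume constant hazards, with progression at 6% per year in the control arm. Use

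F = h/(h + d) × (1 − exp(−5(h + d)))

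and take the subdistribution HR at 5 years as log(1 − F1)/log(1 − F0), where h is the progression hazard, d the hazard of other-cause death, and F0 and F1 are the control and comparison arms.

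| Cause-specific HR | Other-cause death per year, control vs comparison arm | F0 | F1 | Subdistribution HR |
|---|---|---|---|---|
| 1.50 | 1% vs 1% | 0.253 | 0.354 | 1.50 |
| 1.50 | 2% vs 2% | 0.247 | 0.346 | 1.50 |
| 1.50 | 1% vs 3% | 0.253 | 0.338 | 1.42 |
| 1.50 | 2% vs 4% | 0.247 | 0.331 | 1.42 |

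The two models diverge only if other-cause mortality differs between arms.

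**The case against.** The best defence is that the item 3 definition and the analysis section agree with each other, so the disease-assessment list reads as an incomplete summary and the intended meaning can be recovered. PSA is measured at every follow-up visit, so a prostate-cancer death with no earlier recorded failure should be rare. This stands as a limit on size. It does not remove the conflict, because the incomplete list sits in the section that formally defines the endpoints.

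On nodes, one can say that failure and first occurrence most naturally mean something that arises after baseline, that nodal irradiation and ADT are provided for pathologically positive nodes and may shrink them, and that positive nodes need not reach 1.5 cm. All fair. A reader might infer that anyone entering with a node of that size is a regional failure at the first post-treatment scan. The documents do not support this: no such scan is scheduled in the article, and the node would have to persist. What remains is that local failure is explicitly restricted to new disease and regional failure is not.

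A reader might also infer that TTP has two conflicting regressions. The article names Cox for TTP specifically and Fine and Gray only generically, so a cause-specific Cox hazard ratio alongside Gray's cumulative incidence is the natural reading and a legitimate pairing. Nothing in the documents suggests that other-cause mortality would differ between the two fractionation arms. This part is a wording note only.

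**Conclusion.** The disease-assessment section is wrong as written on three counts: it omits two kinds of progression event that the endpoint list includes, it leaves extra-pelvic nodal relapse unclassified by site, and it has no baseline reference for regional failure. The first conflict is confined to prostate-cancer deaths without earlier recorded failure and to new treatment other than ADT given before any other event. The second affects regional failure and distant metastasis far more than TTP. The third is possible, but its frequency is unknown.

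Three stronger readings should be set aside. The two progression definitions are not wholly incompatible, since one contains the other. The article does not call TTP the main efficacy endpoint; it is a secondary endpoint. Distant metastasis is not necessarily understated by the full share of extra-pelvic nodal first relapses, because that requires that none of those patients later shows hematogenous spread.

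The EPIC co-primary analyses, the sample size and the EPIC-based interim rule do not depend on any of this. The correction is still worth making, because the affected endpoints are compared separately between arms and the repair is specific.

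**What to change.** - Replace the progression entry in Definition of disease assessments with the item 3 definition, so that it includes prostate-cancer death and any new unplanned anticancer treatment.
- Extend distant metastasis to include nodal disease outside the pelvis.
- Require that a pelvic node counted as regional failure be new or enlarging relative to baseline. The screening pelvic MRI in Table 2 supplies the reference.
- As a minor wording point, state that the TTP hazard ratio comes from a cause-specific Cox model, with Gray's cumulative incidence for description.

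The cost is the rewording and re-classification of any events already recorded, preferably by someone unaware of treatment arm. No treatment, visit or sample-size change follows.
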